### 3. STUDY DESIGN

This is a multicenter center-stratified block-randomized controlled clinical trial in which POEM will be compared with EBD as first-step treatment for children with achalasia. The primary endpoint will be measured at 12 months after initial treatment. Treatment outcome will be evaluated by a blinded end-point committee (PROBE design). (56)

### 4. STUDY POPULATION

#### 4.1 Population (base)

Treatment naïve pediatric patients (age from 7 up to 17 years inclusive) diagnosed with achalasia type I or II, based on Eckardt score > 3 AND HRM pattern consistent with achalasia.

#### 4.2 Inclusion criteria

In order to be eligible to participate in this study, a subject must meet all of the following criteria:

- Eckardt score > 3
- presence of a HRM pattern consistent with achalasia type I or II according to the latest Chicago classification (CC) criteria
- Age 7 years up to 17 years inclusive

#### 4.3 Exclusion criteria

A potential subject who meets any of the following criteria will be excluded from participation in this study:

- Achalasia type III (this extremely rare subtype in children that is accompanied by esophageal spasm and associated complaints has a worse prognosis compared to type I and II. Literature and expert-opinion based recommendations suggest to treat type III with POEM. Randomizing these patients to EBD with a high a priori risk of relapses is therefore considered unethical)
- Previous surgical or endoscopic achalasia treatment
- Previous surgery of the upper gastrointestinal tract
- Known coagulopathy
- Known Liver cirrhosis and/or esophageal varices
- Known LA grade  $\geq$ B esophagitis
- Known Barrett's esophagus
- Known pregnancy at time of treatment
- Stricture of the esophagus
- Known presence of malignant or premalignant esophageal lesions
- Hiatal hernia > 1cm based on HRM measurement
- Extensive, tortuous dilatation (>7cm luminal diameter, S shape) of the esophagus
- Barium esophagram suggestive of other pathologies

#### **4.4 Sample size calculation**

A recent retrospective review of 21 pediatric achalasia patients, of which 12 received POEM and 9 EBD, reported treatment success (Eckardt score  $\leq$  3) at 12, 24 and 36 months follow-up to be 100% for POEM at all follow up moments and 66.7% vs 44.4% vs 33.3% at 12, 24 and 36 months follow-up for EBD patients respectively.(16) However, in this study no repeated EBD-treatment was allowed in case of clinical recurrence. In adults 76% of patients treated according to our protocol had clinical success after 12 months.(54) Age is known to be a factor in predicting

success-rates of EBD with worse outcome in younger patients.

Taken all this together, we assumed a success rates of 72.5% for EBD and 92.5% for POEM in children after one year, we estimated that with 56 patients in each group, the study would have 80% power to detect a significant difference in success rate between EBD and POEM with a two-sided alpha level of 0.05. To cope with an estimated 10% loss to follow-up, we aim to enroll a total number of 126 patients (63 patients in each group). It is assumed that patient enrollment will be accomplished within 5 years, after approval from all local institutional review boards (IRBs).

## 5 TREATMENT OF SUBJECTS

### 5.1 Investigational product/treatment

In this study, the investigational treatment is POEM. This procedure is performed as described by Inoue et al.(5) For a detailed description of the procedure see under Methods, Section 4.

'Initial therapy' is defined as:

- POEM: a single POEM procedure
- EBD: a series of two EBD sessions, scheduled two weeks apart (see page 29 for allowed variations from the study schedule).
  - In case of *persisting* symptoms as evaluated 7 days after the second EBD session, a third EBD session (35mm in children <12 years; 40mm in children ≥12 years old) will be performed 2-4 weeks after the second. Persisting symptoms in this regards are defined as an Eckardt score >2. Note that a lower score is considered positive (as compared to diagnosis / relapse) due to the fact that the evaluation of weight loss within a week after treatment is considered inaccurate.
  - In case of *relapse* (defined as recurrent symptoms (Eckardt score >3) and evidence of active disease on barium esophagram and/or HRM), a second series of two EBD 2-4 weeks apart will be performed as part of the initial therapy. For this second series a 30 & 35mm balloon is used in children <12 years and a 35 & 40mm balloon is used in children ≥12 years old).

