### ***Esophageal Balloon Dilation (EBD)***

In this study EBD will be performed by experienced (pediatric) gastroenterologists that have independently performed at least 15 procedures. The procedure will be recorded on video to make evaluation afterwards possible. Pictures to evaluate LA grade of GERD will be taken.

Patients will be treated under general anesthesia with endotracheal intubation.

Patients are asked to use a diet with fluids starting at least 48 hours before the procedure, only clear fluids starting 24 hours and nil per mouth starting 8 hours before the procedure.

Initial EBD treatment will consist of a series of two dilatation sessions, scheduled two weeks (10-18 days) apart. In the first session, two dilations of one minute each with a dilatation pressure of respectively 5 and 8 psi will be performed using a single-use low-compliance 30 mm balloon under radiological guidance. The second treatment session is identical but with a larger balloon with a diameter size of 35mm. Patients are discharged without any diet restriction.

If patients in the EBD treatment arm have persisting symptoms, a subsequent dilation with a 35-mm balloon is performed. If a patient has a relapse (recurrent symptoms and evidence of active disease on barium esophagram and/or HRM) a second series of two EBD sessions is performed. This is considered **part of the initial EBD** treatment. If symptom recurrence occurs after a third EBD or second series of two EBDs, this is considered as 'treatment failure'.

Relapse therapy will then be offered at the discretion of local preferences of the attending physician.

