**Table 2: accepted variations from the study schedule:**

| Study moment | Accepted variations |
|--------------|---------------------|
|--------------|---------------------|

|                                                      |                                                               |
|------------------------------------------------------|---------------------------------------------------------------|
| Second EBD session (part of primary therapy)         | 1 – 6 weeks after first EBD session                           |
| T=3 months follow-up                                 | -2 weeks, + 4 weeks                                           |
| T=6 months follow-up                                 | +/- 6 weeks                                                   |
| Monthly measurement of weight in the first 12 months | +/- 2 weeks. A maximum of 25% missed measurements is allowed. |
| HRM, pH-MII and EGD at T=12 months                   | +/- 6 weeks                                                   |
| Cessation of PPI prior to measurements               | - at least 14 days before pH-MII
- 4 – 6 weeks before EGD  |

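### For children of 12 years and over, sections 5.1 and 6.3 give different balloon sizes for the third dilation in the EBD arm

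*Protocol*

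**What the plan says.** Section 5.1 defines initial EBD therapy as two sessions, with a third if symptoms persist (Eckardt score above 2) seven days after the second. For that third session it says "a third EBD session (35mm in children <12 years; 40mm in children ≥12 years old) will be performed", at two to four weeks from the second.

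The EBD text in section 6.3 describes the procedure as it is to be carried out. The first session uses a 30 mm balloon and the second a 35 mm balloon. For the next step it says "If patients in the EBD treatment arm have persisting symptoms, a subsequent dilation with a 35-mm balloon is performed". It gives no age limit and does not refer back to section 5.1. It then counts symptom recurrence as treatment failure only after a third dilation or a second series of two.

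On the gap between the first two sessions, section 6.3 has "scheduled two weeks (10-18 days) apart" and Table 2 has "1 – 6 weeks after first EBD session". Section 5.1 describes "a series of two EBD sessions, scheduled two weeks apart (see page 29 for allowed variations from the study schedule", so it points the reader to the tolerances.

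**The concern.** Both sections address the same patients, the same trigger and the same session. An endoscopist treating a child of 12 or over who works from section 6.3 would repeat the diameter used at session two. One who works from section 5.1 would move to a larger balloon. Each would comply with one section and depart from the other.

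Three things are at stake:

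- **Comparator.** The third session belongs to the randomised EBD strategy, so its content is part of what POEM is compared with.
- **Safety.** Complications are a secondary outcome, and the protocol names perforation as a risk of EBD. Instructions on device size in children should not conflict.
- **Adherence.** Sections 6.1.1 and 6.4 say how the primary endpoint is estimated when a patient does not adhere to the protocol. Under the present text, a reader cannot tell which balloon is adherent for these children.

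**Working it through.** **Step 1: the instructions side by side.**

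| Step in the EBD arm | Section 5.1 | Section 6.3, EBD text | Conflict? |
|---|---|---|---|
| Sessions 1 and 2 | no sizes given | 30 mm, then 35 mm | no |
| Third session, under 12 years | 35 mm | 35 mm | no |
| Third session, 12 years and over | 40 mm | 35 mm | **yes** |
| Second series after relapse | 30 and 35 mm under 12; 35 and 40 mm from 12 | no sizes given | no |

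The last row rests on "For this second series a 30 & 35mm balloon is used in children <12 years and a 35 & 40mm balloon is used" in section 5.1. Section 6.3 mentions the second series without sizes, so nothing there contradicts it. The conflict is confined to one cell. Eligibility runs from 7 to 17 years inclusive, so the affected ages are 12 to 17.

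**Step 2: how many children.** Section 4.4 plans 63 patients per arm. The protocol does not give the share who will need a third session. Assuming 10% to 30%:

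- 0.10 × 63 = 6.3, about 6 children
- 0.30 × 63 = 18.9, about 19 children

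These counts cover all ages. The affected number is lower by the children under 12, whose share is not given either.

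**Step 3: how much the EBD success rate matters to the design.** This point does not dispute the sample size, and the planned figure reproduces. The inputs from section 4.4 are EBD success 0.725, POEM success 0.925, two-sided alpha 0.05 and power 80%. With pooled variance under the null and mean proportion 0.825:

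n = [1.960 × √(2 × 0.825 × 0.175) + 0.842 × √(0.725 × 0.275 + 0.925 × 0.075)]² / 0.20²

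= [1.053 + 0.436]² / 0.04 = 55.5, rounded up to 56 per arm. Power at 56 is 80.4%. Allowing for 10% loss, 56 / 0.9 = 62.2, rounded up to 63.

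With POEM held at 92.5% and 56 per arm, the same method gives:

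| EBD success | Power |
|---|---|
| 70% | 87.3% |
| 72.5% (planned) | 80.4% |
| 75% | 71.4% |

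This shows only that the design is sensitive to the EBD rate. It does not estimate what the balloon conflict would do, because the protocol gives no success or perforation rate by balloon size.

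**Step 4: the interval.** The section 6.3 range is 10 to 18 days. Table 2 allows 1 to 6 weeks, which is 7 to 42 days. The first range lies wholly inside the second, so a session on schedule under section 6.3 is always acceptable under Table 2. The two can be read together as a target and a tolerance.

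**The case against.** The strongest reply is that the defect is small. It concerns one conditional session in one age group, and everything else about the balloons is consistent. That is correct. A reader might infer that the EBD arm is not one defined treatment, but the table above does not support it: the first series, the second series and the third session under 12 are each stated without contradiction.

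A reader might also infer a second contradiction in the interval between sessions. The protocol largely answers this. Section 5.1 sends the reader to the allowed variations, and Table 2, headed as accepted variations, has a row for the second EBD session. What remains is that section 6.3 states its own range without pointing to Table 2.

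The endpoint rule does not depend on balloon size either. Section 5.2 defines failure by symptoms plus barium or manometry evidence, and a blinded committee assesses it. So the definition of the primary outcome is not ambiguous. What could shift is the rate at which EBD patients meet it.

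Finally, randomisation is stratified by centre and section 8 adjusts for stratification factors. This helps only in part. A centre term absorbs differences common to both arms. A difference in balloon practice touches the EBD arm alone, so the centre term would not remove it.

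None of this resolves the conflict in balloon size, for which the protocol offers no reading that satisfies both sections.

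**Conclusion.** The point holds in narrow form. For children of 12 years and over whose symptoms persist after the second session, section 5.1 requires 40 mm and section 6.3 requires 35 mm, and the protocol gives no precedence. The step is part of initial EBD therapy and precedes the counting of failure, so uneven practice could affect the comparator's failure and complication rates.

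The textual conflict rests on no assumption. The count of 6 to 19 children does: it takes an assumed 10% to 30% needing a third session and overstates the affected group, because it includes those under 12. The protocol does not show that the conflict would raise or lower EBD success, perforation risk or power by any given amount, and none is claimed. The correction is warranted because investigators cannot comply with both instructions in a multicentre trial in children.

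**What to change.** - Reconcile sections 5.1 and 6.3 so that the same balloon-size rule for the third session, including any age limit, stands in both. Which rule is right is for the sponsor to decide.
- Notify all participating centres of the reconciled text.
- Check that the case report form records the balloon diameter of each session. The form is not shown, so it may already do so.
- Minor: in the EBD text of section 6.3, add a pointer to Table 2, so that 10 to 18 days is clearly the target and 1 to 6 weeks the accepted tolerance, if that is the intent.

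No outcome analysis by balloon size is needed. Size would depend on age and on symptoms after randomisation, so such a breakdown would be confounded and would cover few children.

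The cost is one clarification letter or amendment and a check of the form. Sample size and analysis are unchanged.

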## 5.2 Retreatment in case of treatment failure

Retreatment is indicated in case of treatment failure, defined as:

- Symptom recurrence: Eckardt score > 3 (see page 31) AND
- Barium esophagram with esophageal stasis at T= 1 minute, and/or HRM (performed if barium esophagram is inconclusive) with IRP4 above upper limits of normal (15mmHg) (39, 40).

These tests are part of standard clinical care and are performed in all achalasia patients who have persisting- or recurrent symptoms after treatment.

Retreatment (LHM, POEM, EBD or intra-sphincteric botox injection) will be offered at the discretion of local preferences and/or the attending physician.

## 6 METHODS

### 6.1 Study parameters/endpoints

#### 6.1.1 Main study parameter/endpoint

Primary outcome measure is the need for any retreatment (also including retreatment that is planned *before* 12 months follow-up, but scheduled *after* 12 months follow-up) (*refer to 5.2 Retreatment in case of treatment failure*). Primary outcome will be evaluated at 12 months follow-up.

If a subject refuses one of the study measurements during follow-up, but is otherwise willing to continue study participation, he/she will remain in follow-up for assessment of primary outcome at t=12 months. In case a patient does not adhere to the protocol, or is lost to follow-up, available data from the last included timepoint are used for estimation of the primary endpoint in an intention to treat analysis.

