#### **6.4 Withdrawal of individual subjects**

Parents and/or patients can redraw subjects from the study at any time for any reason if they wish to do so without any consequences. The investigator can decide to withdraw a subject from the study for urgent medical reasons.

If a subject refuses one of the study measurements during follow-up, but is otherwise willing to continue study participation, he/she will remain in follow-up for assessment of primary outcome at  $t=12$  months. In case a patient does not adhere to the protocol, or is lost to follow-up, available data from the last included timepoint are used for estimation of the primary endpoint in an intention to treat analysis.

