#### **6.5 Follow-up of subjects withdrawn from treatment**

If a subject gets withdrawn from the study, he/she will have the standard achalasia care, depicted in figure 1. In case of treatment failure after study withdrawal, therapeutic approach will be decided based on shared decision making and the discretion of the attending physician.

If a subject refuses one of the study measurements during follow-up, but is otherwise willing to continue study participation, he/she will remain in follow-up.

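### The last-timepoint rule for the primary endpoint counts unobserved months as free of retreatment, which can only lower the failure rates and shifts the odds ratio when loss differs by arm

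*Protocol*

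**What the plan says.** Protocol section 6.1.1 defines the primary outcome as the need for any retreatment, assessed at 12 months and including retreatment planned by then but carried out later. For patients who do not adhere or are lost, it states that "available data from the last included timepoint are used for estimation of the primary endpoint in an intention to treat analysis". Section 6.4 repeats the sentence.

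Under section 5.2 a failure needs two things: an Eckardt score above 3, and evidence on the barium esophagram and/or manometry. Under section 6.3 (Esophageal Balloon Dilation), recurrence in the EBD arm counts as failure only after a third dilation or a second series of two; POEM is a single procedure.

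Section 8 analyses the endpoint by logistic regression, reporting an odds ratio adjusted for stratification factors. It names no other handling of missing outcomes. Section 4.4 anticipates the losses: "To cope with an estimated 10% loss to follow-up", the target is 126 patients, 63 per arm. The loss is given overall and not by arm.

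**The concern.** Carrying the last value forward is a poor match for a cumulative event. A child last seen at month 3 without a recorded failure contributes no retreatment for all 12 months, although months 3 to 12 were never observed. The error runs one way: a failure that happens after the last contact is missed, and none is added. The filled-in values are then analysed as if observed, so the confidence interval carries no allowance for them.

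The comparison is at stake as well as the two rates. Treatment is open to families and clinicians (only the endpoint committee and central readers are blinded), so loss related to treatment or outcome is plausible. Because EBD failure needs more steps before it can be declared, EBD failures may come later, and equal loss could hide more of them in that arm.

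The sentence also places non-adherent patients under the same rule without saying whether outcomes observed after non-adherence are used. Intention to treat requires that they are.

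**Working it through.** **Inputs from section 4.4.** "we assumed a success rates of 72.5% for EBD and 92.5% for POEM in children after one year", so failure is 27.5% and 7.5%; "with 56 patients in each group, the study would have 80% power", "with a two-sided alpha level of 0.05"; 10% loss; 63 enrolled per arm.

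**Assumptions (not in the protocol).** The split of loss by arm; the share *f* of lost patients' failures that was recorded before loss (*f* = 0 is the worst case); and lost patients having their own arm's failure risk.

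**1. The plan's own figures.** With the pooled-variance formula and no continuity correction,

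n = [1.96·√(2·0.175·0.825) + 0.8416·√(0.275·0.725 + 0.075·0.925)]² / 0.20² = 55.5, so 56 per arm.

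56 / 0.9 = 62.2, so 63 per arm and 126 in all. Both figures reproduce.

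**2. Effect of the rule.** With true risk p and loss L, observed failure = p(1 − L) + L·p·f. All 63 per arm stay in the denominator. The true odds ratio (EBD vs POEM) is (0.275/0.725)/(0.075/0.925) = 4.68.

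Power below is exact for the two-sided chi-square test without continuity correction. The adjusted logistic regression may differ slightly.

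| Loss EBD / POEM | f | Observed failure | Difference (points) | Odds ratio | Power, 63 per arm |
|---|---|---|---|---|---|
| 0 / 0 | – | 27.5% vs 7.5% | 20.0 | 4.68 | 86.2% |
| 10 / 10 | 0 | 24.75% vs 6.75% | 18.0 | 4.54 | 81.5% |
| 15 / 5 | 0 | 23.4% vs 7.1% | 16.3 | 3.98 | 73.6% |
| 15 / 5 | 0.5 | 25.4% vs 7.3% | 18.1 | 4.32 | 80.6% |
| 5 / 15 | 0 | 26.1% vs 6.4% | 19.8 | 5.19 | 87.7% |
| 20 / 0 | 0 | 22.0% vs 7.5% | 14.5 | 3.48 | 64.2% |

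For example, in the second row 0.275 × 0.9 = 0.2475 and 0.075 × 0.9 = 0.0675. The fair comparator for power is the planned 56 evaluable per arm, which gives 82.7% by the same exact method. At equal 10% loss the rule therefore costs about one point of power.

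**3. No true difference (27.5% in both arms), f = 0.**
- 10/10 loss: 24.75% in both arms, type I error about 5%.
- 15/5 loss: 0.275 × 0.85 = 23.4% vs 0.275 × 0.95 = 26.1%, a false difference of 2.75 points; type I error about 6.4%.
- 20/0 loss: 22.0% vs 27.5%, a false difference of 5.5 points; type I error about 11.0%.

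**4. Unequal loss does not always move the risk difference.** With 3% EBD / 11% POEM loss and f = 0: 0.275 × 0.97 = 26.7% and 0.075 × 0.89 = 6.7%. The difference stays at 20.0 points, but the odds ratio becomes 5.09.

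**5. Later EBD failures, as an illustration.** With 10% loss in both arms, f = 0.25 for EBD and 0.5 for POEM: 0.275 × (0.9 + 0.025) = 25.4% and 0.075 × (0.9 + 0.05) = 7.1%. The odds ratio is 4.45, compared with 4.61 if f were 0.5 in both arms.

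**The case against.** The best defence is that the effect is small at the loss the protocol expects. That stands: about 2 points of difference at worst, about one point of power, and an odds ratio of 4.54 against 4.68. Every larger figure rests on assumed splits, mostly in the worst case; with half of the lost patients' failures already recorded, the 15/5 case keeps 80.6% power. A separate analysis plan may also add sensitivity analyses, but the primary rule is fixed in the protocol.

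A reader might infer more than the text supports:

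- *Every lost patient is scored a success.* No. A failure recorded before loss is kept, and Eckardt scores are collected monthly. A patient last seen with a score above 3 but not yet tested is left undefined.
- *Outcomes after non-adherence are discarded.* The protocol does not say so. The preceding sentence in 6.1.1 keeps patients who refuse a measurement in follow-up to month 12. The wording is unclear; it is not a stated departure from intention to treat.
- *Children withdrawn after a procedural complication are turned into successes.* Section 6.4 says only "The investigator can decide to withdraw a subject from the study for urgent medical reasons". Complications are a separate secondary outcome, and section 7.3.2 follows patients withdrawn for an adverse event after they leave. Counting such withdrawals as failures would change the endpoint.
- *Section 6.5 lets later failures go uncounted.* "In case of treatment failure after study withdrawal, therapeutic approach will be decided based on shared decision making" describes care, and is silent on data.
- *Section 4.4 contradicts the rule.* Enrolling 63 to allow for loss is an ordinary margin and is compatible with analysing all 63.

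**Conclusion.** The rule is wrong as written for this endpoint. It counts unobserved follow-up as event-free wherever no failure is on record, it can only lower the observed failure rates, and it presents unknown outcomes as known.

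Unequal loss is not the dividing line for bias. Equal loss already shrinks a true difference, while under no true difference equal loss does no harm; and some unequal splits leave the risk difference intact. What does follow is that unequal loss can push the odds ratio, the planned effect measure, in either direction: to 3.98 or 5.19 instead of 4.68 under the assumed 15/5 and 5/15 splits, or to a type I error of 6.4% to 11% under no true difference.

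At the stated 10% loss, if equal and unrelated to outcome, the damage is modest. It becomes material if loss is larger, unequal or related to outcome, and the protocol gives no basis for excluding that. That EBD failures are hidden more often is plausible from how failure is declared in that arm, but the timing of failures is not given.

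**What to change.** Replace the sentence in both 6.1.1 and 6.4 with:

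> All participants are analysed as randomised, using all observed retreatment data to month 12 regardless of adherence; retreatment status of withdrawn participants is obtained from routine achalasia care where consent allows. For participants whose 12-month status remains unknown, it is multiply imputed within arm, using the last observed Eckardt score and time of last contact, and analysed with the planned logistic regression; a tipping-point analysis and the last-timepoint rule are sensitivity analyses.

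This names one primary estimator and keeps the odds ratio of section 8. Imputation assumes that loss is explained by the variables in the model, which is why the tipping-point analysis belongs beside it. Only about five POEM failures are expected (0.075 × 63 = 4.7), so the imputation model has to stay small.

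The cost is some analysis work, the effort of retrieving outcomes, and slightly wider confidence intervals. Withdrawn patients remain in standard achalasia care under section 6.5, so a source exists. Enrolment stays at 126.
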